### Study schedule

The measurements that need to be performed at each visit are listed in Table 2.

**Table 2 T2:** Study schedule of clinical trial (6 months)

	**Initial screening**		**Treatment times**		**Follow-up**	
	**Visit 1**	**Visit 2**	**Visit 3**	**Visit 4**	**Visit 5**	**Visit 6**
	**Week 0**	**Week 1**	**Week 2**	**Week 4**	**Month 2**	**Month 5**
Determined the exclusion criteria	Yes					
Informed consent	Yes					
Randomized	Yes					
Weight	Yes		Yes	Yes		
Blood pressure	Yes		Yes	Yes		
Heart rate/Rhythm	Yes		Yes	Yes		
Respiratory rate	Yes		Yes	Yes		
Spurling’s test	Yes					
Brachial plexus force test	Yes					
Drug allergy history	Yes					
Blood routine	Yes			Yes		
Urine routine	Yes			Yes		
Excrement routine	Yes			Yes		
Occult blood	Yes			Yes		
ECG	Yes			Yes		
Liver function test	Yes			Yes		
Kidney function test	Yes			Yes		
X-ray (frontal and lateral)	Yes			Yes		
Concomitant medication		Yes	Yes	Yes		
VAS scores	Yes	Yes	Yes	Yes	Yes	Yes
NDI scores	Yes		Yes	Yes	Yes	Yes
SF-36 scores		Yes	Yes	Yes		
The medicine issue		Yes	Yes			
Compliance assessment			Yes	Yes		
Degree of satisfaction				Yes		
Safety evaluation		Yes		Yes		

ECG: Electrocardiogram; VAS: Visual analogue scale; NDI: Neck disability index: SF-36: The MOS item short from health survey.

### Assessment of adverse events

All subjects are to be questioned regarding adverse events during treatment at each visit; all reported adverse events will be analyzed in spite of the investigators’ assessments of causality and will be categorized according to the Medical Dictionary for Regulatory Activities (MedDRA, Version 8.1J).

### Sample size considerations

We calculated the sample size for this two arm trial on the basis of the comparison treatment (Qishe Pill) versus placebo, with equal allocation in the treatment arms and five repeated measurements (at entry, at 2 and 4 weeks’ treatment, and at 2 and 5 months’ follow-up), with an estimated correlation coefficient of the measurements of ρ=0.8 and a difference in the mean value of the VAS for neck pain of 12 mm, as a clinical relevant difference with an estimated standard deviation in each treatment group of 25 mm [10]. As neck pain is the main complaint in cervical radiculopathy, we chose this outcome to calculate the sample size. Under the setting of alpha = 0.05 and power = 90%, the calculated sample size of each group is around 96. Considering 20% loss to follow-up, the total sample size needed to detect this difference at a 5% level of significance with a power of 90% is 240 patients.

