### Statistical analysis

The data will be collected and analyzed according to the intention-to-treat principle. Standard statistical techniques will be used to describe characteristics of patients in both groups. We will compare baseline characteristics in both groups and if incomparability appears, we will perform the secondary analysis, adjusting for differences. The primary outcome, amount of pain, will be compared between both groups using survival analysis and analysis of variance for repeated measures. If adjustment for possible baseline incomparability is needed, analysis of covariance will be performed. We will use multivariate analysis to do retrospective analysis with the baseline data of the effective cases and ineffective cases in the treatment group. Differences in the baseline data will be used to optimize the inclusion criteria. We will do subgroup analysis based on severity of pain (VAS=70 mm) and use of analgesics.

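### The stated repeated-measures inputs do not give 96 per group under the usual two-sided tests, so the 90% power is not tied to the planned analysis

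*Protocol article*

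**What the plan says.** The section Sample size considerations describes a two-arm comparison with equal allocation. It counts "five repeated measurements (at entry, at 2 and 4 weeks" of treatment and at 2 and 5 months of follow-up, so the entry value is one of the five. The other inputs are "an estimated correlation coefficient of the measurements of ρ=0.8", "a difference in the mean value of the VAS for neck pain of 12 mm" as the clinically relevant difference, and the spread, "with an estimated standard deviation in each treatment group of 25 mm". The result is given as: "Under the setting of alpha = 0.05 and power = 90%, the calculated sample size of each group is around 96". Loss to follow-up of 20% is then added, and the total needed "at a 5% level of significance with a power of 90% is 240 patients".

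The section Statistical analysis compares the primary outcome by survival analysis and "analysis of variance for repeated measures". Analysis of covariance is reserved for the case that the groups turn out not to be comparable at baseline. Neither section says whether alpha is one- or two-sided, or which contrast (group effect, group-by-time, or one visit) the 90% refers to.

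**The concern.** All the numerical inputs are printed, so the figure can be checked against its own stated basis. If 96 does not follow from five measurements and a correlation of 0.8, the 90% belongs to some other test, and the reader cannot tell what power the planned repeated-measures analysis has.

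The choice of contrast matters because entry is listed among the five measurements. Randomisation makes the expected group difference at entry zero. A group effect averaged over all five levels therefore dilutes the 12 mm, while an analysis that adjusts for entry gains a great deal from the high correlation. The same 96 completers can be too few for one analysis and far more than enough for another.

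**Working it through.** **Inputs from Sample size considerations:** difference 12 mm, SD 25 mm, correlation 0.8, five measurements including entry, alpha 0.05, power 90%, loss 20%, allocation 1:1.

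**Assumed here:** two-sided test, the same correlation between all pairs of visits (compound symmetry), and 12 mm at every post-baseline visit unless stated otherwise.

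**Step from 96 to 240.** 96/0.8 = 120 per arm, and 2 × 120 = 240. This step is correct as written.

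**Single visit, correlation ignored.** n = 2 × (1.960 + 1.2816)² × (25/12)² = 2 × 10.507 × 4.340 = 91.2, so 92 (93 with the t distribution).

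**Repeated-measures contrasts.** Multiply 91.2 by the variance factor of the contrast, and adjust for any change in the difference.

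| Contrast | Variance factor | n per group (normal; t) | Power at 96 per group |
|---|---|---|---|
| Mean of five, 12 mm throughout | (1 + 4×0.8)/5 = 0.84 | 76.6 → 77; 78 | about 95% |
| Mean of four post-baseline visits | (1 + 3×0.8)/4 = 0.85 | 77.5 → 78; 79 | about 95% |
| Mean of five, zero difference at entry | 0.84, difference 12×4/5 = 9.6 mm | 119.7 → 120; 121 | about 82% |
| Change from entry, one visit | 2×(1 − 0.8) = 0.40 | 36.5 → 37; 38 | above 99.9% |
| Change from entry, mean of four | 0.85 + 1 − 1.6 = 0.25 | 22.8 → 23; 24 | above 99.9% |
| Adjusted for entry, one visit | 1 − 0.64 = 0.36 | 32.8 → 33; 34 | above 99.9% |
| Adjusted for entry, mean of four | 0.85 − 0.64 = 0.21 | 19.2 → 20; 21 | above 99.9% |
| Single visit, correlation ignored | 1 | 91.2 → 92; 93 | about 91% |

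The third row in full: the variance of the mean is 625 × 0.84 = 525, so n = 2 × 10.507 × 525/9.6² = 119.7.

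**Group-by-time.** For a difference of 0 at entry and 12 mm at the four later visits, the squared deviations from the mean of 9.6 sum to 9.6² + 4 × 2.4² = 115.2. The noncentrality is (n/2) × 115.2/(625 × 0.2) = 0.461n on 4 numerator degrees of freedom, and 90% power needs 35 per group. Other time profiles tried gave 28 to 46.

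**Where 96 could come from.**
- Single visit: 92 to 93. Dividing 91.2 by the Wilcoxon efficiency 3/π = 0.955 gives 95.5, but the article mentions no rank test.
- Mean of five, already inflated for loss: 76.6/0.8 = 95.8. The later inflation to 120 per arm would then be a second one, and 2 × 96 = 192 would have been the total.
- One-sided 5%, mean of five with zero difference at entry: 98.

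**The case against.** The best defence is that 96 can be reached from every printed input. The mean-of-five formula at a correlation of 0.8 gives 76.6, and dividing by 0.8 for loss gives 95.8. A one-sided 5% test with entry averaged in gives 98, close enough to the article's approximate figure. The article also condenses a fuller protocol, where the formula may stand.

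Part of this holds. A reader might infer that no repeated-measures test can give 96, or that the correlation and the five measurements played no part in it. The document supports neither inference: both routes just named use those inputs, and the single-visit explanation gives 92 to 93, not 96.

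The defence does not rescue the figure as printed. The text adds the 20% loss after reaching 96, so the first route means that loss was counted twice. Nothing in the article indicates a one-sided test. The absence of a formula is not the complaint. The complaint is that the stated result does not follow from the stated inputs under the usual two-sided tests. Rounding does not cover the gap: 96 is 17 to 19 above the 77 to 79 for the averaged contrasts and 24 below the 120 with entry diluted in.

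A second objection is that 96 completers are ample for most analyses. That is right, and it limits the conclusion.

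**Conclusion.** The figure of 96 per group at 90% power does not follow from its stated repeated-measures basis under the usual two-sided tests, and the article does not settle whether it came from a single-visit calculation or from a figure already inflated for loss.

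It would be tempting to conclude that the trial is underpowered. The document does not show that. The 82% requires three things together: the group main effect decides, entry is one of the averaged response levels, and the difference there is zero. The article lists entry among the five measurements but names no contrast for the ANOVA. The other two-sided tests in the table give 91% to above 99.9% at 96 completers per arm, and if loss was counted twice the trial is larger than its own calculation required.

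These figures rest on two-sided 5%, compound symmetry at 0.8, and a constant 12 mm after entry. The last assumption matters, since treatment lasts 28 days and two of the four later measurements are at months 2 and 5. If the difference ran 12, 12, 6, 0 mm, its post-baseline mean would be 7.5 mm and about 200 per group would be needed for that contrast.

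**What to change.** Keep 240. Go back to the original calculation and state the contrast, sidedness and formula behind 96. If the 20% loss was already in 96, say so and correct the double counting in the text. Then restate size and power for the contrast that decides the trial. For example:

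*Two-sided 5%; group difference in the mean of the four post-baseline VAS values; 12 mm, constant over visits; SD 25 mm; correlation 0.8 between all visits. 78–79 completers per group give 90% power. With 120 randomised per group and 20% loss, 96 completers per group give about 95%, and more with adjustment for the entry value.*

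In Statistical analysis, use the entry VAS as a covariate, or name group-by-time as the deciding contrast. Do not average entry as a response level in the ANOVA group effect. Making entry a planned covariate goes beyond an arithmetic correction, because the article now keeps covariance analysis for baseline incomparability, so it should be fixed before unblinding.

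The cost is one rewritten paragraph and one added sentence, with no change in enrolment.

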### Statistical analysis

The data will be collected and analyzed according to the intention-to-treat principle. Standard statistical techniques will be used to describe characteristics of patients in both groups. We will compare baseline characteristics in both groups and if incomparability appears, we will perform the secondary analysis, adjusting for differences. The primary outcome, amount of pain, will be compared between both groups using survival analysis and analysis of variance for repeated measures. If adjustment for possible baseline incomparability is needed, analysis of covariance will be performed. We will use multivariate analysis to do retrospective analysis with the baseline data of the effective cases and ineffective cases in the treatment group. Differences in the baseline data will be used to optimize the inclusion criteria. We will do subgroup analysis based on severity of pain (VAS=70 mm) and use of analgesics.

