## Methods/design

### Study design

This clinical trial is a multi-center, randomized, double-blind, placebo-controlled design. Participants will be enrolled by clinic recruitment at five hospital sites (Longhua Hospital, Shanghai University of TCM; Huadong Hospital, Fudan University; Affiliated Hospital of Changchun University of TCM; TCM Hospital of Gansu province; and TCM Hospital of Suzhou city). Participants will be recruited in equal numbers (n=48) from each of the five sites.

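### Baseline adjustment depends on an observed imbalance, with no criterion or covariate named, and it is unclear whether ANCOVA supplements or replaces the primary result

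*Protocol article*

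**What the plan says.** Two sentences in the protocol article, Statistical analysis, govern baseline adjustment. The first is "We will compare baseline characteristics in both groups and if incomparability appears, we will perform the secondary analysis, adjusting for differences". The second, placed after the primary comparison, is "If adjustment for possible baseline incomparability is needed, analysis of covariance will be performed". Neither gives a test, a threshold or a covariate.

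Between them stands the primary comparison: the amount of pain "will be compared between both groups using survival analysis and analysis of variance for repeated measures". The term to be tested (group, or group by time) is not named.

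Sample size considerations assumes "an estimated correlation coefficient of the measurements of ρ=0.8" and builds on "five repeated measurements (at entry, at 2 and 4 weeks’ treatment, and at 2 and 5 months’ follow-up", so the entry value counts as one of the five measurements. The target is "a difference in the mean value of the VAS for neck pain of 12 mm", with SD 25 mm in each group. Outcome measurements and Table 2 show that VAS and NDI are both collected at baseline.

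**The concern.** In a randomised trial a baseline difference between arms is a chance event. Its size says nothing about which variables predict the outcome, so it is a poor guide to what to adjust for. The plan nevertheless lets the observed baseline table decide whether ANCOVA is run. When nothing is flagged, which is the usual case, a strongly prognostic covariate that is already in hand may go unused.

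The two sentences also sit badly together. One calls the adjusted analysis secondary. The other says ANCOVA is performed when needed, directly after the primary comparison. A reader cannot tell which result would be primary once an imbalance is seen. At stake are the precision of the primary estimate and a primary result that is fixed before the data are seen.

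**Working it through.** **Inputs.** From Sample size considerations: difference 12 mm, SD 25 mm, ρ=0.8, alpha 0.05, power 90%, about 96 per arm, 20% loss, 240 in total. Assumed here: a two-sided test, the same SD and the same correlation at all times (entry included), and an effect of 12 mm at each of the four post-baseline times.

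**1. The plan's own figure.** n per arm = 2(1.960+1.282)² × 25²/12² = 91.2, so 92 (93 with the t distribution), against about 96 in the plan. Then 96/0.80 = 120 per arm, or 240, which matches exactly. The 96 is close to an ordinary two-sample calculation and shows no gain from ρ=0.8.

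**2. Precision by type of comparison.** The variance of the difference between arms is f × 2 × 25²/n. At ρ=0.8 and n=96:

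| Comparison | f | SE (mm) |
|---|---|---|
| One time, unadjusted | 1 | 3.61 |
| One time, change from entry | 2(1−ρ) = 0.40 | 2.28 |
| One time, ANCOVA | 1−ρ² = 0.36 | 2.17 |
| Mean of four, unadjusted | (1+3ρ)/4 = 0.85 | 3.33 |
| Mean of four minus entry | 0.85+1−2ρ = 0.25 | 1.80 |
| Mean of four, ANCOVA | 0.85−ρ² = 0.21 | 1.65 |

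Variance saved by ANCOVA:
- against the unadjusted comparison: 1−0.36 = 64% (one time) and 1−0.21/0.85 = 75% (mean of four);
- against the change contrast: 1−0.36/0.40 = 10% (one time) and 1−0.21/0.25 = 16% (mean of four).

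At an assumed ρ of 0.5, the single-time factors are 1.0 (unadjusted), 1.0 (change) and 0.75 (ANCOVA), so the saving is 25% against either.

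**3. Power at 96 per arm.**
- One time, unadjusted: 12/3.61 = 3.33, and Φ(3.33−1.96) = 91%.
- Group main effect with entry among the five responses: the effect is diluted to 12 × 4/5 = 9.6 mm. The variance factor is (1+4ρ)/5 = 0.84, so the SE is 3.31 mm. Then 9.6/3.31 = 2.90, and Φ(2.90−1.96) = 83%.
- Group by time with entry included (simulated, 1,500 trials): about 100% for 12 mm. For a 6 mm effect it is 74%, against 95% for ANCOVA on the mean of four and 42% for the unadjusted mean of four.

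**4. Carry-over of an unflagged gap.** Assume a baseline SD of 25 mm, a 5% test as the trigger, and 120 per arm compared. The baseline SE is 25√(2/120) = 3.23 mm, and the largest gap not flagged is 1.96 × 3.23 = 6.3 mm. The expected shift is:
- unadjusted post-baseline comparison: 0.8 × 6.3 = about 5 mm (0.5 × 6.3 = about 3 mm at ρ=0.5);
- change contrast: (0.8−1) × 6.3 = about −1.3 mm, in the opposite direction.

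**5. Error rate of a two-step rule** (simulated, one time, ρ=0.8, no effect, 5% test of baseline VAS as trigger). Adjusting only when the test is significant gives 3.0% type I error. The unadjusted test alone has about 5% overall, but 44% in the trials where baseline VAS is flagged. Claiming success on either result gives 8.7%.

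**The case against.** The strongest objection is that repeated-measures ANOVA may already use baseline. Sample size considerations counts entry among the five measurements. If the tested term is group by time, each patient serves as their own control, and at ρ=0.8 most of the baseline information is used. This stands. A reader might infer that the plan throws away most of the precision implied by ρ=0.8, but the documents do not support that without naming the test term. The 64% to 75% holds only against an unadjusted post-baseline comparison.

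Other stronger readings also fail:
- **An underpowered trial.** The unadjusted single-time comparison keeps about 91% power for 12 mm. Only the group main effect with entry included falls below 90%.
- **Inflated type I error.** Mechanical test-then-adjust is conservative (3.0%). The 8.7% needs a rule allowing success on either result, which the article does not state.
- **Two declared primary answers.** One sentence calls the adjusted analysis secondary, so the text supports only that it is unclear which result is primary.
- **A biased estimate.** The 5 mm shift is conditional on an observed gap. Over repeated randomisations the unadjusted estimate is unbiased.
- **Site missing from the model.** Study design sets 48 patients per site, but Randomization and allocation states no stratification by site, and a condensed article may leave such covariates to the full plan.

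It can also be said that thresholds, covariates and the test term belong in an analysis plan that is not shown. That is fair for the detail. It does not excuse the rule itself, which the article states.

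**Conclusion.** The point holds for the conditional rule and for the unclear standing of ANCOVA. Its size is a range. At ρ=0.8, always adjusting for baseline VAS saves about 10% of the variance in the least favourable case (single-time change contrast) and 75% in the most favourable (unadjusted mean of four post-baseline times). ANCOVA did at least as well as the alternative under every reading tried. The plan's power target is met on the single-time and group-by-time readings and missed (83%) on the group main effect with entry included. These figures rest on the plan's ρ and SD, equal correlation and SD over time, and a two-sided test. The carry-over figures also assume a baseline SD of 25 mm and a 5% trigger, neither of which the article gives. The change is worth making because it improves precision at almost no cost and removes a data-dependent choice.

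**What to change.** Replace both conditional sentences in Statistical analysis with:

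> The primary repeated-measures model uses the post-baseline VAS values as responses and always includes baseline VAS as a continuous covariate, with the primary treatment contrast (term and time point) fixed in advance; the NDI analysis likewise includes baseline NDI. Baseline characteristics are described only and do not determine the covariates.

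Entry must leave the response set. Otherwise baseline would appear both as response and as covariate, and a group main effect would still be diluted. The wording covers the repeated-measures comparison only; the survival analysis named beside it needs its own specification.

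The cost is wording and one covariate degree of freedom per model. The data are already collected. Trial status reports two sites at 28 and 30 enrolled, short of the planned 48, so on that status the change could still be made before unblinding.

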### Interventions

At randomization, patients will be assigned to receive Qishe Pill (or matching placebo) at 3.75 g twice per day. In this study, the same outer packing will be used for both Qishe Pill and the matching placebo. Therefore, the treating physicians, participants and investigators will be blinded to treatment assignment. The Qishe Pill and matching placebo used in the trial are both manufactured and provided by a pharmaceutical company that meets the requirements of Good Manufacturing Practice. All significant medicine information, including ingredient composition, heavy metals, etc., is provided by the same company.

Follow-up visits will be continued for 5 months. At each visit, data will be collected on the outcome events, compliance and adverse reactions leading to a discontinuation of study medications. All primary and secondary events will be documented and be centrally adjudicated with the use of standardized definitions.

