### Outcome measurements

The primary study outcome is pain severity (measured with a visual analogue scale (VAS)). Secondary outcomes are a composite of functional status (measured by NDI), patient satisfaction, and adverse events as reported in the trial. The VAS measures the amount of pain, which is a pain score ranging from 0 (no pain) to 100 mm (very severe pain) [9]. Operationally, the VAS score is displayed as a horizontal line, 100 mm in length, with word descriptors anchored at each end. The patient marks on the line the point that they feel represents their perception of their current pain. The VAS score is then determined by measuring in millimeters from the left hand end of the line to the point that the patient marks. The VAS score and NDI will be measured at all the measurement points (baseline, 2 and 4 weeks of treatment duration, and 2 and 5 months of follow-up duration).

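### The primary VAS comparison is given to two methods with no rule for which decides, no event is defined for the survival analysis, and no visit or contrast is named as primary

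*Protocol article*

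**What the plan says.** Under Outcome measurements the endpoint is a score: "The primary study outcome is pain severity (measured with a visual analogue scale (VAS"). It is read in millimetres at "baseline, 2 and 4 weeks of treatment duration, and 2 and 5 months of follow-up duration". Table 2 also shows a Week 1 VAS reading that this section does not list.

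Under Statistical analysis: "The primary outcome, amount of pain, will be compared between both groups using survival analysis and analysis of variance for repeated measures". The same section adds "If adjustment for possible baseline incomparability is needed, analysis of covariance will be performed" and describes the adjusted analysis as secondary. It also says "The data will be collected and analyzed according to the intention-to-treat principle".

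Under Sample size considerations the trial is sized on a difference in mean VAS with "five repeated measurements (at entry, at 2 and 4 weeks’ treatment, and at 2 and 5 months’ follow-up"), and the number is then raised: "Considering 20% loss to follow-up".

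The only wording about outcome events is under Interventions: "All primary and secondary events will be documented and be centrally adjudicated with the use of standardized definitions". No event is defined there or elsewhere in the article.

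**The concern.** A survival analysis needs an event, a time origin and a censoring rule. The primary outcome as defined is a continuous score at fixed visits and supplies none of these. The two methods are joined without an order, an alpha split or a statement that both must succeed.

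The repeated-measures ANOVA is not tied to a contrast either. It could be judged on the group effect averaged over visits, on the group-by-time term, or on one visit. These answer different questions here, because treatment lasts 28 days and two of the four post-baseline visits (months 2 and 5) come after it.

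At stake is what counts as a positive trial. If this is settled after the data are seen, the 5% significance level no longer describes the procedure.

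**Working it through.** **Inputs.** From Sample size considerations: difference 12 mm, SD 25 mm, correlation 0.8, alpha 0.05 (taken as two-sided; the article does not say), power 90%, about 96 per group, 20% loss, 240 in total. From Outcome measurements: four post-baseline visits.

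**1. Which analysis does the stated size belong to?**
- Single-visit comparison of means: n = 2 × (1.960 + 1.282)² × (25/12)² = 91.2, so 92 per group.
- Mean of all five readings: variance factor (1 + 4 × 0.8)/5 = 0.84, so 77 per group.
- Mean of the four post-baseline readings: factor (1 + 3 × 0.8)/4 = 0.85, so 78 per group.
- The stated 96 is not reproduced by any of these. The last step is exact: 96/(1 − 0.2) = 120 per group, 240 in total.
- No event rate, hazard ratio or event count appears. The calculation gives the survival analysis no support and does not identify the deciding contrast.

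**2. Type I error under the two readings of the word joining the methods.**
- Either method suffices, tests independent: 1 − 0.95² = 0.0975. Under any dependence the ceiling is 0.05 + 0.05 = 0.10.
- Both methods required: the error cannot exceed that of either test, so at most 0.05.
- Simulation under no effect (5,000 runs per threshold, 120 per arm, SD 25, correlation 0.8, event assumed to be the first VAS drop of at least 12, 20 or 30 mm): the test on the mean of the post-baseline visits alone 4.6 to 5.2%, log-rank alone 5.0 to 5.3%, either one significant 9.6 to 10.1%. The thresholds are assumptions, because the article gives none.

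**3. Why the contrast matters (96 per group, two-sided 5%, normal approximation).**
- One visit with a 12 mm effect: SE = 25 × √(2/96) = 3.61; power = Φ(12/3.61 − 1.96) = 91%.
- Mean of four post-baseline visits, constant 12 mm: SE = 25 × √(0.85 × 2/96) = 3.33; power = Φ(12/3.33 − 1.96) = 95%.
- The same mean if the effect were 12, 12, 6, 0 mm (an assumption): mean 7.5 mm; power = Φ(7.5/3.33 − 1.96) = 62%.
- That assumed profile with the entry reading averaged in as a zero difference: mean 30/5 = 6.0 mm, SE = 25 × √(0.84 × 2/96) = 3.31; power = Φ(6.0/3.31 − 1.96) = 44%.
- Constant 12 mm after entry, with entry averaged in: mean 48/5 = 9.6 mm; power = Φ(9.6/3.31 − 1.96) = 83%.

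Averaging over visits can therefore help or hurt, depending on how the effect evolves. Averaging in the entry reading lowers power under both profiles.

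**4. Incomplete patients.** 0.20 × 240 = 48, leaving 192, or 96 per group. This is the most that a complete-profile ANOVA would remove at the planned loss.

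**The case against.** The article condenses a fuller protocol, and an analysis plan may exist. Repeated VAS readings can be turned into time to a threshold, so survival analysis is not impossible. The reference to standardised event definitions, and the mention of effective and ineffective cases, may point to a response definition held elsewhere. This stands as far as it goes: the supportable statement is that no event is defined in this article. It does not remove the point, because the article does state the primary analysis, and what it states does not match its own outcome or sample size.

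Four stronger readings are tempting and are not supported:

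- **That the ANOVA will drop incomplete patients and so contradicts intention-to-treat.** The article does not say so. Imputation or a mixed-model fit is not excluded, and handling of missing values is commonly left to the analysis plan. The planned enlargement also already covers a 20% loss as far as power goes.
- **That type I error is inflated.** This needs the reading in which either method alone suffices. The text is equally open to requiring both.
- **That the best of several visits could be chosen.** No visit-by-visit testing is stated, so an error rate for that procedure does not describe this plan.
- **That the effect will be diluted.** The 62% and 44% figures depend on the assumed decline after treatment stops. A constant effect gives about 95% for the four-visit mean.

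Nor should the adjudication sentence simply be struck out. Adverse events are a listed secondary outcome and may be what it refers to.

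**Conclusion.** The point holds in limited form. One continuous primary outcome is assigned to two methods without an order; one of them has no event defined in the article and no basis in the sample size; and no visit, average or model term is named as deciding. The error consequence ranges from no more than 5% (both required) to about 9.75% (either suffices, tests independent). Loss of up to 48 of 240 patients, and the tension with intention-to-treat, arise only if the ANOVA is fitted on complete profiles. The power figures show that the choice of contrast matters; they do not predict a loss of power. Because the gap determines what the trial can conclude, it should be closed before unblinding.

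**What to change.** - Remove survival analysis from the primary comparison. Alternatively, define its event, time origin and censoring rule, and make it secondary.
- Name one primary analysis: a likelihood-based mixed model for repeated measures on the post-baseline VAS of all randomised patients, with baseline VAS as a covariate rather than one of the averaged outcomes. State which scheduled visits enter.
- Name one deciding contrast and make the others secondary. The end-of-treatment (Week 4) difference is one candidate. The post-baseline average is another if long-term efficacy is the question, since the Background criticises earlier studies for measuring only short-term effects. The sponsor should choose and say why.
- Under Interventions, clarify which events are adjudicated and keep the sentence for those.

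The cost is wording only, with no extra patients or data. The sponsor gives up a second route to a positive result.
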